## Abstract

**Introduction:**

Depression and alcohol use disorders are international public health priorities for which there is a substantial treatment gap. Brief mental health interventions delivered by lay health workers in primary care services may reduce this gap. There is limited economic evidence assessing the cost-effectiveness of such interventions in low-income and middle-income countries. This paper describes the proposed economic evaluation of a health systems intervention testing the effectiveness, cost-effectiveness and cost-utility of two task-sharing approaches to integrating services for common mental disorders with HIV and diabetes primary care services.

**Methods and analysis:**

This evaluation will be conducted as part of a three-armed cluster randomised controlled trial of clinical effectiveness. Trial clinical outcome measures will include primary outcomes for risk of depression and alcohol use, and secondary outcomes for risk of chronic disease (HIV and diabetes) treatment failure. The cost-effectiveness analysis will evaluate cost per unit change in Alcohol Use Disorder Identification Test and Centre for Epidemiological Studies scale on Depression scores as well as cost per unit change in HIV RNA viral load and haemoglobin A1c, producing results of provider and patient cost per patient year for each study arm and chronic disease. The cost utility analyses will provide results of cost per quality-adjusted life year gained. Additional analyses relevant for implementation including budget impact analyses will be conducted to inform the development of a business case for scaling up the country’s investment in mental health services.

**Ethics and dissemination:**

The Western Cape Department of Health (WCDoH) (WC2016_RP6_9), the South African Medical Research Council (EC 004-2/2015), the University of Cape Town (089/2015) and Oxford University (OxTREC 2–17) provided ethical approval for this study. Results dissemination will include policy briefs, social media, peer-reviewed papers, a policy dialogue workshop and press briefings.

**Trial registration number:**

PACTR201610001825405.

Strengths and limitations of this studyThis study will provide some of the first empirical evidence of the cost-effectiveness of integrating services for common mental disorders in the primary care offering for HIV and diabetes.The study will generate findings that may guide priority setting through application of quality-adjusted life year-based outcomes and decision-making around the implementation of mental health counselling within the health system.This paper adds to the growing body of protocols for economic evaluations conducted alongside randomised controlled trials.As health service use is self-reported, there is a possibility for recall bias, to limit this, a 1-month recall period will be used for ambulatory services and a 6-month recall for hospitalisation, and hospitalisations will be validated through the Department of Health Data Centre.The 1-year follow-up period may reflect outcomes that do not fully represent the full benefit that patients and the health system could gain through the availability of this service; further work using an extended follow-up period may be proposed.

## Introduction

Common mental disorders (CMDs) including depression, anxiety and alcohol use disorders are highly prevalent conditions that impose a significant societal cost and impact on quality of life.^1^ Globally, these conditions have been shown to be the leading cause of non-fatal burden of disease.^1 2^ The disabling impact of these conditions is particularly significant in patients suffering from chronic physical conditions.^3^ CMD comorbidity has been shown to exacerbate major modifiable risk factors for chronic disease; contribute to chronic disease progression; increase the prevalence of preventable complications and disability; result in poor adherence and ultimately lead to treatment failure.^1 4^ There is a plethora of evidence on the impact of depression and alcohol use disorders on diabetes outcomes.^5 6^ Likewise, alcohol consumption and depressive conditions have been associated with poor HIV outcomes.^7 8^ In addition, high-income country (HIC) evidence suggests that patients with these multimorbidities have higher healthcare costs even after adjusting for the costs of mental healthcare^9^; suggesting potential cost savings from investing in mental health treatment for patients with multimorbidities.^10^

There is a pressing need for evidence on cost-effective strategies for integrating mental healthcare into primary health services, particularly in low-income and middle-income countries (LMICs), where health systems are typically fragile and chronically underfunded. In these health systems, an investment in mental health services at primary care level for patients with chronic disease has the potential to result in significant returns on investment due to reduced chronic disease treatment costs. South Africa—with the world’s largest ART programme,^11^ an increasing prevalence of diabetes^11^ and a huge unmet need for CMD treatment^12^—is one LMIC that may benefit from this integrated approach.

Task-sharing^13 14^ involves redistributing tasks from specialist providers to non-specialist health workers,^15^ with specialists providing ongoing support to these health workers. Task-sharing is a common strategy for the provision of primary care services in constrained LMIC settings.^16^ Due to the long lead times in training mental health staff and financial resource limitations, the task-sharing discourse has found appeal in the policy discussions around introducing and expanding mental healthcare in LMICs.^1 17^ These discussions are centred on using task-shared approaches^18^ to upskill lay health workers to integrate mental health services such as brief counselling interventions into primary care.^19 20^ Task-sharing the psychosocial counselling of patients who have chronic comorbidities to lay health workers is a particularly appealing and potentially cost-effective strategy to treat patients and support their adherence to chronic medication^21 22^ and therefore limit overall health system costs of care.^4 16^

While task-sharing the treatment for CMDs from mental health professionals to lower level healthcare workers has been suggested as an effective way to deliver services within the context of scarce human resources^4^ and has been shown to be cost-effective in some HIC settings, there is little if any economic evidence to support the implementation of such strategies in LMICs.^4 16^ This lack of evidence limits decision making around the allocation of resources for these services. Economic evidence on the institutional investment, cost-effectiveness and budget impact of this approach is necessary for empirically informed health service planning.^23^ This work presents a protocol of a cost-effectiveness (CEA) and cost-utility analysis (CUA) from a societal perspective (ie, providers and patients) of a task-shared mental health counselling intervention for patients with comorbid HIV or diabetes in South Africa.

## Methods and analysis

### Patient and public involvement

Patients and the public were engaged with through the trial, and were not directly involved in this study.

### Trial design

This study is nested in Project MIND, a cluster randomised controlled trial across 24 public primary care facilities.^24^ Myers *et al*
24 describe the trial in detail. The trial will compare the effectiveness of treatment as usual (MIND_TAU) and two alternative methods for integrating a psychosocial intervention into the primary care services for HIV and diabetes. Treatment as usual (TAU) is representative of typical primary care level services for CMD in the South African public health service facilities, which is typically limited to referrals.^25 26^ The two models will be the dedicated and designated models of care. In the dedicated approach (MIND_DED), community health workers (CHWs) will be hired and added to the facility staff complement and will dedicate their time to *only* delivering the new counselling service. In the designated approach (MIND_DES), CHWs already working in the facility will be designated to deliver the service *in addition* to their other chronic disease-related activities such as adherence counselling for HIV and health promotion. Supervision and debriefing of all the counsellors in the active arms will be task-shifted to registered psychological counsellors in line with the national mental health policy framework.^27^ Descriptions of the CHWs and registered psychological counsellors roles in the MIND-DED and MIND-DES models and their qualifications and skills levels are detailed in the trial protocol.^24^

#### Intervention and comparator

The counselling programme delivered in MIND-DED and MIND-DES is based on motivational interviewing (MI) and problem solving therapy (PST).^28^ It is delivered in three sessions over 6 weeks with one optional booster session. The MI component provides psychoeducation about depression and hazardous alcohol use in relation to chronic disease, builds readiness for counselling and helps participants develop goals for counselling. The PST component targets maladaptive coping strategies and builds skills and strategies for dealing with life problems. Patients will receive individual face-to-face counselling from CHWs and take-home booklets to support self-learning between sessions. Registered psychological counsellors, supervised by psychologists, will train the counsellors.^24^ The underlying theory, content and evidence for the efficacy of the counselling approach for reducing symptoms of depression and hazardous/harmful alcohol use over the 1-year time frame have been described previously.^29–31^ In the TAU arm, the standard package of care will be provided to patients who are suspected of having mental health problems. In general, patients using the HIV or diabetes service are asked by a nurse or doctor attending to their care about their mental well-being, life stressors and use of alcohol or other substances. Patients are provided with advice to change their lifestyles. Where the healthcare provider deems it necessary, patients are referred to a mental health nurse for further assessment or screening. The patient may also be referred to a social worker who may refer them to non-governmental organisations (NGOs) who provide counselling and support services.^24^

#### Outcome measures

The primary outcomes for the trial are measures of psychosocial functioning, specifically changes in self-reported risk of depression as measured by the Centre for Epidemiological Studies scale on Depression (CES-D)^32^ and self-reported hazardous alcohol use as measured by the Alcohol Use Disorder Identification Test (AUDIT).^33^ Secondary outcomes include biological measures aimed at assessing changes in chronic disease treatment response, specifically haemoglobin A1c (HbA1c) for diabetes and HIV-1 RNA viral loads for HIV. Other secondary outcome measures include self-reported adherence to chronic disease medication and health-related quality of life (HRQoL) measured using the EuroQol-5D (EQ-5D).^34^ All outcomes are measured longitudinally at baseline, and at 6 and 12 months follow-up assessments, recruitment on the trial started in 2017 and will end in February 2019 and final outcome assessments will end in 2020 (figure 1).

**Figure 1 F1:**
[figure not shown]
Economic evaluation: analyses, outcomes, measurement and assessment timing. AUDIT, Alcohol Use Disorder Identification Test; BMI, body mass index; CEA, cost-effectiveness analysis; CES-D, Centre for Epidemiological Studies scale on Depression; CUA, cost- utility analysis; EQ-5D, EuroQol-5D; HbA1c, haemoglobin A1c; QALY, quality-adjusted life year.

#### Sample size and patient population

Recruitment will be restricted to consenting adult patients who meet criteria for hazardous alcohol use or depression using the AUDIT or CES-D. These patients are already diagnosed and receiving treatment for diabetes or HIV, but not currently receiving treatment for a CMD. The trial requires a sample size of 1200 patients (600 with HIV and 600 with diabetes) to detect reductions in hazardous alcohol use and risk of depression at 12-month follow-up. The sample size calculations are based on a cluster randomised design with two active arms and a control arm. This clinical trial is powered to detect clinical outcomes, specifically reductions hazardous/harmful alcohol use and risk of depression at 12-month follow-up rather than economic outcomes.^24 35^

### MIND economic evaluation

#### Objective

The study will be a prospective economic evaluation. The objectives include estimating:Full economic provider costs of the mental health intervention; any cost offsets attributable to the intervention related to changes to the costs of HIV or diabetes care at the primary care level and changes to the costs of referral care (including tuberculosis (TB), emergency department and inpatient care).Patient costs: associated with the intervention which will include direct out-of-pocket payments to private health providers (consultations and medications, etc), travel and subsistence costs and productivity losses.Cost-effectiveness in terms of the incremental cost per unit of improvement in disease-specific outcome (CES-D, AUDIT, HIV-1 RNA, HbA1c).Cost-utility in terms of the incremental cost per quality-adjusted life year (QALY) gained.Budget impact of scaling up the intervention.

To achieve these objectives, the incremental cost-effectiveness ratio (ICER) will be calculated by ordering the MIND_DED, the MIND_DES and MIND_TAU alternatives from least cost to highest cost and calculating the difference in costs and outcomes against the next less costly, non-dominated alternative or against the common baseline of MIND_TAU.

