### Estimating costs for the provider’s perspective

Within economic evaluation, the appropriate scope of provider costs includes all costs incurred within the intervention and any changes in broader health system costs that can be attributable to the intervention. We have categorised these costs as intervention costs, HIV and diabetes service costs and other related provider costs. As shown in table 1, our approach to estimating these costs entails the measurement of quantities of resources that are used, and multiplying these quantities by the value (or unit cost) of each resource. These separate steps of measurement and valuation are described below.

**Table 1 T1:** Measuring and valuing provider costs

Cost component	Measurement		Valuation	
	Resources used	Quantities or utilisation	Valuation data	Allocation factor
Intervention				
Capital costs				
Facility readiness workshops	Number of staff	Time from trial data	Cost of employment converted to annual equivalent cost	DED/DES/TAU headcount
Intervention training for counsellors	Number of counsellors	Time from trial data	Cost of employment converted to annual equivalent cost	DED/DES/TAU headcount
Counselling room	Space	Square metres	Replacement value converted to annual equivalent cost	DED/DES/TAU headcount
Furniture and equipment	Tape recorders	Inventory	Replacement value converted to annual equivalent cost	DED/DES/TAU headcount
Vehicles	Vehicles	Inventory	Replacement value converted to annual equivalent cost	DED/DES/TAU headcount
Recurrent costs				
Counselling personnel	Number of staff (lay counsellors; registered counsellors; clinical psychologist)	Time from time and motion tool	Cost of employment×proportion of time	DED/DES/TAU headcount
Counselling supplies	Manuals, notebooks, pens	Number used—from trial data	Market value	DED/DES/TAU headcount
Non-intervention personnel	Number of staff	Time from facility data	Cost of employment×proportion of time	Facility headcount
Utilities	Electricity, water, other utilities, phone, cleaning, transport and stationery	Facility utilisation	Annual facility expenditure	Facility headcount
HIV/Diabetes service				
Capital costs				
Buildings	Space used for HIV/diabetes service	Square meters	Replacement value converted to annual equivalent cost	HIV/Diabetes headcount
Equipment and furniture	Equipment and furniture used for HIV/diabetes service	Inventory	Replacement value converted to annual equivalent cost	HIV/Diabetes headcount

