### Budget impact analysis

There is an increased demand from decision makers in both LMIC and HIC settings for estimates of the real fiscal implications of investing in health services within a defined budget and budgetary period.^53 54^ Trial-based estimates of intervention uptake and population-based estimates of numbers in need of the intervention will be used in budget impact approximations,^55^ which will be conducted using a mathematical programming approach.^56 57^ Mathematical programming provides a useful equity lens for informing policy decisions around the provision of care in high burden, high cost contexts.^58^ It will involve analysing alternative implementation strategies with differing equity implications subject to a budget constraint. This approach aims to support policy making by applying principles of constrained maximisation in resource allocation.^58^ The estimates from this study will inform policy-level discussions on the fiscal implications of investing in primary care mental health services.

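### No cost of finding patients by AUDIT/CES-D is named; if routine DED/DES delivery needs that screening, the intervention cost, the budget impact and the ICER against TAU are understated

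*Protocol article*

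**What the plan says.** **Entry.** The section on sample size sets the entry rule for all three arms: "Recruitment will be restricted to consenting adult patients who meet criteria for hazardous alcohol use or depression using the AUDIT or CES-D".

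**Usual care.** Under Intervention and comparator, a nurse or doctor generally asks HIV and diabetes patients about well-being, stressors and substance use. Then: "Where the healthcare provider deems it necessary, patients are referred to a mental health nurse for further assessment or screening". Systematic use of AUDIT or CES-D is not described.

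**Intervention.** The same section says of the counselling programme: "It is delivered in three sessions over 6 weeks with one optional booster session". Screening is not described as a component.

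**Cost scope.** The first objective is "Full economic provider costs of the mental health intervention". The provider-cost section adds: "the appropriate scope of provider costs includes all costs incurred within the intervention and any changes in broader health system costs". The latter count where the intervention causes them.

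**Cost items.** The intervention block of Table 1 lists readiness workshops, counsellor training, counselling room, furniture and equipment, vehicles, counselling personnel, counselling supplies, non-intervention personnel and utilities. Measurement of resource use adds a time and motion tool for counsellor time spent delivering the intervention.

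**Volume inputs for scale-up.** "Trial-based estimates of intervention uptake and population-based estimates of numbers in need of the intervention will be used in budget impact approximations".

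**The concern.** The effects that enter the ICER come from patients selected by a positive screen. A health service adopting either active model has to find such patients, and in doing so will screen attenders who turn out negative. That work is additional to usual care as the article describes it, but no cost line names it.

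Two stated outputs depend on it directly: the full cost of the intervention and the budget impact. The budget impact is the more exposed, because it starts from numbers in need, whereas screening effort grows with everyone attending. A third output depends on it conditionally. Under Determining cost-effectiveness, the provider-perspective cost per QALY is compared with a threshold, and an omitted positive cost in the active arms would favour both models against usual care.

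**Working it through.** **1. Is the cost named anywhere?** The article gives no screening cost, yield or time, so there is no figure to reproduce. The check is a reading of each place where the cost could appear.

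| Place | What it covers | Case-finding named? |
|---|---|---|
| Table 1, counselling personnel | Lay counsellors, registered counsellors, psychologist | No |
| Table 1, counselling supplies | Manuals, notebooks, pens | No |
| Table 1, non-intervention personnel | Facility staff time, allocated by facility headcount | No |
| Table 1, remaining intervention rows | Workshops, training, room, equipment, vehicles, utilities | No |
| Time and motion tool | Counsellor time in delivery, active arms | No |
| Table 2 | Discount rate, utility weights, unit costs, missing data, utilisation, outcomes | No |
| Budget impact | Uptake and numbers in need | No |

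**2. Direction.** Let c be the net cost per attender screened, over and above any usual questioning or nurse screening it replaces. Let p be the share of those screened who are positive and accept counselling, and dE the effect gain over TAU.

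- Case-finding cost per counselled patient = c/p.
- Change in the ICER against TAU, if charged to the active arms only = (c/p)/dE. This is positive when c > 0 and dE > 0.
- Change in the ICER against TAU, if charged equally to all three arms = 0.
- Change in the cost difference between DED and DES, if both screen alike = c/p − c/p = 0.
- Budget impact for N attenders: counselling costs N × p × k, with k the counselling cost per patient. Screening adds N × c, which does not shrink when fewer attenders are in need.

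**3. Illustrative size.** Only the three sessions come from the article. Assumed: p = 10% to 50%, 5 to 15 minutes per screen, 30 to 60 minutes per session.

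- Screens per counselled patient, 1/p: 1/0.5 = 2 to 1/0.1 = 10.
- Screening minutes per counselled patient: 5/0.5 = 10 to 15/0.1 = 150.
- Counselling contact: 3 × 30 = 90 to 3 × 60 = 180 minutes.
- Extremes of the ratio: 10/180 = 6% and 150/90 = 167%.
- Middle case (p = 20%, 10 minutes per screen, 45 minutes per session): 10/0.2 = 50 minutes against 3 × 45 = 135, or 37%.
- Effect of yield: halving p to 10% in the middle case doubles screening to 10/0.1 = 100 minutes, or 74%.

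These are ratios of staff contact minutes. The intervention cost also includes supervision, training, workshops, room, vehicles and supplies, so the proportionate effect on cost would probably be smaller.

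**The case against.** **All arms are screened at recruitment.** A reader might infer that screening is a cost only active-arm patients generate, so that the ICER is certainly too low. The documents do not support that. Entry criteria apply to TAU participants as well, and a recruitment cost charged to every arm cancels. The ICER effect therefore needs a further premise: that routine DED/DES would screen systematically and routine TAU would not. The stated aim of informing decision makers about introducing the service makes that premise reasonable, but the article does not state it. Cancellation in any case does not help the intervention cost or the budget impact.

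**Usual care already does some case-finding.** This stands. Only the increment over clinician questioning and discretionary nurse screening should be charged.

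**Screening may be a research procedure, or already covered.** AUDIT and CES-D appear as eligibility criteria and outcomes, and the article does not say who screens; the trial protocol it cites may. A personnel row could hold the time. So a reader cannot conclude that screening is costed at zero. However, the time and motion tool is described only for delivery of counselling, and the non-intervention personnel row is spread by facility headcount, which would not attribute screening to the active models.

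**The article is condensed.** This carries little weight for Table 1, which the valuation section offers as the detailed account of data sources and allocation factors and which itemises down to pens. It carries more for the budget impact, where only volume inputs are named and unit costs are not listed.

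**Conclusion.** The omission is established: case-finding is named in no cost row, measurement method, sensitivity analysis or budget input, although the plan claims full provider cost.

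The bias is conditional on two points the article leaves open: that routine DED/DES delivery depends on AUDIT/CES-D screening beyond what TAU does, and that no existing personnel line captures the time. If both hold, the intervention cost and the budget impact are understated, and the ICER against TAU is too low when the QALY gain is positive. The budget impact is the strongest part. DED versus DES is largely unaffected provided both screen in the same way.

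The size is not estimable from the documents. The range of 6% to 167% of contact time shows only how strongly the answer depends on yield and minutes per screen. It is not an estimate, and no effect on the threshold decision has been shown.

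**What to change.** 1. State whether AUDIT/CES-D screening is part of the DED/DES service or a research procedure only, and who would do it in routine care.
2. If it is part of the service, add a recurrent case-finding row to the intervention block of Table 1: minutes per screen divided by screening yield, valued at the cost of employment of the screening cadre. Charge it to DED and DES as the increment over the questioning and referral described for TAU.
3. Add a number-to-screen input to the budget impact, so that screening scales with HIV and diabetes attenders and counselling with screen-positives who accept.
4. In Table 2, report the ICER with and without screening cost, varying yield and minutes per screen. If screening is regarded as research only, say so and keep the with-screening result as a scenario.

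The cost is one extra row, one extra budget input, counts of patients screened and eligible, and a time per screen. The downside is a less favourable ICER and budget impact, and an assumption about which cadre screens.
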